# Study protocol of a factorial trial ECHO: optimizing a group-based school intervention for children with emotional problems

**DOI:** 10.1186/s40359-021-00581-y

**Published:** 2021-06-21

**Keywords:** Indicated prevention, Anxiety, Depression, Factorial design, MFS, Digital interventions, Parental involvement, Children, Effectiveness, Implementation

## Abstract

**Background:**

Youth mental health problems are a major public health concern. Anxiety and depression are among the most common psychological difficulties. The aim of this study is to evaluate an optimized version of a promising indicated group intervention for emotional problems. The program (EMOTION Coping Kids Managing Anxiety and Depression) targets school children 8–12 years with anxious and depressive symptoms and examines three factors. Factor 1 compares the standard EMOTION intervention delivered in 16 group-based sessions (Group), versus a partially-digital EMOTION intervention (DIGGI) delivered as eight group sessions and eight digital sessions. Both versions use virtual reality technology (VR) to improve behavioral experiments. Factor 2 compares parent participation in a 5-session parent group (high involvement) versus sharing information with parents via a brochure (low involvement). Factor 3 compares the use of a measurement and feedback system (MFS) designed to help group leaders tailor the intervention using feedback from children with no MFS.

**Methods:**

Using a cluster-randomized factorial design, 40 schools across Norway will be randomized to eight different experimental conditions based on three, two-level factors. To assess internalizing symptoms in children, children and their parents will be given self-report questionnaires pre-, post-, and one year after intervention. Parents also report on demographics, user satisfaction, personal symptoms and perception of family related factors. Teachers report on child symptoms and school functioning. Group leaders and the head of the municipal services report on implementation issues. The primary outcomes are changes in depressive and anxious symptoms. Some secondary outcomes are changes in self-esteem, quality of life, and user satisfaction. Questions regarding the consequences of the COVID-19 pandemic are included. Treatment fidelity is based on checklists from group leaders, and on user data from the participating children.

**Discussion:**

This study is a collaboration between three regional centers for child and adolescent mental health in Norway. It will provide knowledge about: (1) the effect of school-based preventive interventions on anxiety and depression in children; (2) the effect of feedback informed health systems, (3) the effect and cost of digital health interventions for children, and (4) the effect of parental involvement.

**Supplementary Information:**

The online version contains supplementary material available at 10.1186/s40359-021-00581-y.

## Background

Mental health problems in children are a major public health concern. Anxiety disorders are among the most common psychological difficulties, with studies indicating that 23.9% of children 6–8 years and 31.9% of adolescents have had an anxiety disorder at some point during their life [1]. Depression is also common, with studies indicating that up to 14.3% of adolescents have had a depressive episode [2]. Yet, anxiety and depression in children often go undetected in the specialist services in Norway [3]. Moreover, subthreshold anxiety and depression, which also considerably reduces daily functioning, may affect even larger numbers of children [4]. From 2015, the responsibility for treating mild to moderate depression and anxiety in Norway shifted from specialized mental health clinics to first line services [5]. There is, therefore, a great need for standardized assessments and interventions in first line services.

### Promising interventions for emotional problems

Developing integrated evidence-based interventions (EBI) that target multiple, but related, emotional problems (i.e., a transdiagnostic approach), has been an important task for the research group involved in the ECHO study. The study uses an optimized version of the EMOTION intervention [6]. The EMOTION intervention is based on cognitive behavioral therapy (CBT) with parental involvement. Our research group recently conducted a randomized controlled trial (RCT), the TIM study, in 36 schools (*N* = *873*) across seven municipalities in Norway [7]. Screening of 1686 children in this study identified 48% with high symptom levels of anxiety or depression. Outcome results were positive and indicated that the intervention can reduce symptoms of anxiety and depression and that the services would benefit from optimized screening and intervention methods [8–10]. International research supports these results [11], reporting medium to large effect sizes (0.38–0.79) for selective and indicated interventions. The same study suggested that further investigation is needed to optimize effects when interventions are transferred into routine practice.

ECHO explores three factors that might optimize effects: (1) combining the psychosocial intervention with a Measurement Feedback System (MFS), (2) combining traditional interventions and internet-based interventions, (3) including parents in the intervention.

#### MFS

In ECHO, group leaders can tailor the intervention for each child through a MFS. New results concerning the registration of personal aims in MFS for adolescents [12] indicate that MFS can support the service provider in enhancing the co-operation with youth and help them stay focused on the aims of the intervention. Results from a Cochrane report [13] on the effect of client feedback identified different MFS instruments that can be used in child health care. These instruments suffer, however, from use of measures that are not well-validated, have a rigid structure, are not adaptable, or are too costly in use for large-scale distribution [14].

#### Internet-based interventions

One of the areas that was highlighted by the group leaders in the TIM study was the overall length of the intervention. Meta-analyses indicate that internet-based interventions that reduce intervention costs have the potential to provide small to moderate effect-sizes when targeting anxious and depressive symptoms within traditional interventions [15]. To explore this further, the ECHO study evaluates the standard version of EMOTION with a revised, digital version (DIGGI) that conducts half of the sessions in an online format.

#### Parental involvement

Involving parents in CBT interventions targeting depression and anxiety in children can have a positive effect on treatment outcomes [16]. Yet, parental involvement has also yielded mixed results [17]. While it may be desirable to include parents in separate parent groups, resources to be able to run these groups are scarce in first line services. It can also be difficult for some parents to attend parent meetings.

The aims of examining these factors are to enable the group leader to tailor the intervention through feedback for the specific child, to facilitate implementation in the services, provide easier access for the children through digital sessions, and make behavioral experiments more accessible and realistic for the children through use of VR technology. Including parents may have the potential to support the intervention directed to the child. Integrating self-directed internet-based sessions along with traditional group meetings and the distribution of self-help materials to parents may reduce costs.

The elements mentioned above have not previously been evaluated together while optimizing an intervention. They constitute three factors and are related components that, properly combined, should form the strongest intervention outcomes. It is therefore useful that our multifactorial design allows for the testing of interactions as well as main effects (factors), in a design with equal distribution of all factors within each main effect [18]. Promising advances are also offered through use of new technology such as internet-based sessions and virtual reality (VR) technology. Behavioural experiments constitute an essential approach in CBT. VR technology that provides realistic situations can facilitate the child’s need for gradual exposure to situations that might otherwise result in avoidance or sadness. Through these VR situations, the group leaders establish stimulus control and similar situations can be rehearsed several times [19]. While not its own factor, the use of VR was included in both versions of the EMOTION intervention (Factor 2) because of its strong potential to improve outcomes.

## Method/design

The present study is a cluster randomized factorial design, with three factors, each with two levels, giving eight different experimental conditions randomized to schools across three regions in Norway: south-east, central, and north. Each of the 40 recruited schools will therefore be randomly assigned to one of the experimental conditions resulting in five schools per condition (see Table 1).

**Table 1 Tab1:** Experimental conditions of ECHO project

	Factor		
Experimental condition number	1. Measurement feedback system (yes/no)	2. EMOTION coping kids (group/DIGGI*)	3. Parental involvement (high/low)
1	Yes	Group	High
2	Yes	Group	Low
3	Yes	DIGGI	High
4	Yes	DIGGI	Low
5	No	Group	High
6	No	Group	Low
7	No	DIGGI	High
8	No	DIGGI	Low

*The group version includes 16 sessions delivered in a group-format. DIGGI is a partially digital version with eight sessions delivered in group-format, and eight sessions delivered as internet-based sessions

The stages of the enrollment, intervention, and assessment can be seen in Table 2.

**Table 2 Tab2:** SPIRIT table for evaluation of the ECHO study

	Study period						
	Enrolment^a^	Allocation^b^	After school allocation: Assessments and Intervention				Close-out
			Pre-I (T1)	Intervention	Post-I (T2)	Post + 1 yr (T3)	
Timepoint	Coh1: Q1 2020	Q1 2020	Coh1: Q1 2020		Coh1: Q2 2020	Coh1: Q2 2021	
	Coh2: Q3 2020	Q3 2020	Coh2: Q3 2020		Coh2: Q4 2020	Coh2: Q4 2021	
	Coh3: Q1 2021	Q1 2021	Coh3: Q1 2021		Coh3: Q2 2021	Coh3: Q2 2022	
	Coh4: Q3 2021	Q3 2021	Coh4: Q3 2021		Coh4: Q4 2021	Coh4: Q4 2022	
	Coh5: Q1 2022		Coh5: Q1 2022		Coh5: Q2 2022		Coh 5: Q2 2023
**Enrolment**							
Eligibility screen^c^			X				
Informed consent	X						
Allocation		X					
**8 interventions**				X			
**Assessments**							
Primary outcomes (MASC & SMFQ)			X^c^		X	X	X
Secondary outcomes except			X		X	X	X
User satisfaction, PIE Stigma evaluation sheet Implementation components					X		X
KIDSCREEN-27, RCADS, attitudes towards EBPs, TWQ, ICS, ILS			X				
Sustainability							X

^a^Enrollment occurs at the beginning of the semester prior to delivery of the intervention. Each cohort represents a group of children recruited during the semester

^b^Allocation (randomization) is conducted at the school-level, therefore allocation reflects when new schools joined the study

^c^Study eligibility for individual children is based on their scores on the MASC and MFQ (primary outcome measures)

*Coh* cohort, *Q* quartile

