School eligibility will be determined by region of the country and municipality. School-size is a recruitment criterion, as the participating schools need to have at least one full class in each grade to increase the probability of recruiting enough children to run an EMOTION group. The study will be presented to key personnel (principals at schools, heads of different primary care health agencies) at each site. The person responsible for each site or health agency will sign a statement of intention to participate in the study, while interested schools will also sign an agreement to participate in the study and are asked to nominate a contact person. The intervention will be offered each semester (autumn/spring term) of each school year. The plan is to include an average of five children from each grade in each school every semester, but group size may vary with between three and seven children per group. The children are screened prior to participation (T1) and assessed after the intervention (T2) (see Table 2). One year after the end of the intervention, the children will complete the same self-report measures to identify possible long-term effects (T3), an important goal for all preventive interventions. Responsibilities of school contacts include informing teachers and parents at the targeted grades about the study and facilitating the completion of the child surveys at the measurement times (T1-T3). Children are presented with age-appropriate oral and written information about the study. Parents are informed about the study during parental meetings and receive a link to detailed written information and electronic consent. Parents are invited to consent on the child`s behalf if they consider that their child has more sad or anxious feelings than peers and the child wishes to participate in a group. Both parents (or one parent with single parent care) must provide a consent before a child can participate. Presentations and videoclips are available to help recruit schools and children. The recruitment of participants is reported in accordance with the Consolidated Standards of Reporting Trials (CONSORT) guidelines for clustered randomized trials [20]. A project webpage (https://www.echo.r-bup.no) is developed to enhance the communication between all participants.

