#### Secondary outcomes

See Table 3.

**Table 3 Tab3:** Table for secondary outcomes in the ECHO study

Instrument	Description
*Beck self-Concept Inventory for Youth* (BSCI-Y)	The BSCI-Y [36] is a 20-item 4-point Likert subscale from *Beck Youth Inventories—Second Edition* (BYI-II). The BSCI-Y subscale measures perceptions about self-competence, potency, and positive self-worth. Reported Cronbach`s alpha for BSCI-Y is .83-.92 [37]
*General Self-Efficacy Scale* (GSE-6)	The GSE-6 is a short-form of the GSE [38], a psychometric scale designed to assess optimistic self-beliefs to cope with a variety of difficult demands in life. The GSE-6 has shown satisfactory validity and reliability with reported Cronbach’s alpha between .79 and .88 [39]
KIDSCREEN-27	The KIDSCREEN-27 [40] is a 27-item scale used to assess generic health-related quality of life. The scale has five dimensions: Physical Well-Being, Psychological Well-Being, Autonomy & Parents, Peers & Social Support and School Environment. Internal consistency values (Cronbach's alpha) range between .79 (Physical Well-being) and .84 (Psychological Well-being) for the different dimensions for the self-report versions [41]
*Revised Child Anxiety and Depression Scale* (RCADS C/P)	The RCADS C/P [31] is a 47-item, children self-report questionnaire. Convergent and discriminant validity tests are favorable, and the measure has showed greater correspondence to specific diagnostic syndromes than traditional measures of anxiety and depression [42]
*Behavior and Feelings Survey* (BFS)	The BFS [27] is a brief, 12-item rating scale designed to facilitate efficient progress-monitoring during youth psychotherapy. Items are rated on a scale from 0 (not a problem) to 4 (a very big problem). Three scale scores can be derived: Internalizing Problems (sum of items 1–6), Externalizing Problems (sum of items 7–12), and Total Problems (sum of items 1–12). Item 1–6 will be used in the MittEcho App
*Stigma and Evaluation sheet*	The *Stigma and Evaluation sheet* [43] measures overall user-satisfaction and participants’ experiences of stigmatization. A Norwegian translation of this 10-item instrument with a 10-point scale is used
*Idiographic aims*	The *Idiographic aims* are based on a self-report assessment tool for adolescents [44] and have been adjusted for use with children in the ECHO study. The instrument enables the respondents to define their most important aims in the MittEcho App to be addressed during sessions

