### Planned statistical analysis

Several models will be run to test for the main treatment outcomes, implementation outcomes, and related research questions.

The analyses will involve changes in outcome variables. A combination of linear mixed models and latent growth curve analyses will be used to identify differences between treatment groups, as well as change rates in growth over time. Based on the experience from the previous study, the rate of missing data due to electronic data collection will be low. Otherwise, missing data will be accounted for using full information maximum likelihood in growth curve analyses and restricted maximum likelihood techniques in mixed effects models where applicable, well-established techniques that allow for the inclusion of all available data.

To investigate the psychometric properties of some instruments initial exploratory factor analyses will be performed to investigate which factors we are able to obtain from our sample. Further, confirmatory factor analysis will be used. Correlations between subscales will be computed using Pearson’s r. Internal consistency for the subscales will be measured with Cronbach’s alpha.

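### Change in quality of life is a named secondary outcome, but Table 2 schedules its only described instrument, KIDSCREEN-27, at baseline only, against text that implies repeated child measures

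*Protocol article*

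**What the plan says.** All places are in the protocol article.

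- **Abstract, Methods.** "Some secondary outcomes are changes in self-esteem, quality of life, and user satisfaction".
- **Secondary outcomes, Table 3.** KIDSCREEN-27 "is a 27-item scale used to assess generic health-related quality of life". The RCADS is in the same table and "is a 47-item, children self-report questionnaire".
- **Table 2 (SPIRIT table), Assessments.** A default row, "Secondary outcomes except", is marked at T1, T2, T3 and close-out. Exception rows follow. One of them, "KIDSCREEN-27, RCADS, attitudes towards EBPs, TWQ, ICS, ILS", is marked at T1 only.
- **Recruitment and eligibility criteria.** One year after the intervention "the children will complete the same self-report measures to identify possible long-term effects (T3").
- **Data management.** Web questionnaires from parents, teachers and children are described at T1, T2 and T3, with no child scale singled out as an exception.
- **Planned statistical analysis.** "The analyses will involve changes in outcome variables".

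**The concern.** An outcome defined as change needs at least one measurement after baseline. The abstract promises change in quality of life, and the analysis section says that change is what will be modelled. The only table that gives timing instrument by instrument provides no later measurement of the one scale that could supply it.

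What is at stake is whether the trial can say anything about the effect of feedback, delivery format or parental involvement on quality of life. A follow-up questionnaire that was not given on time cannot be recovered. Someone building the T2 and T3 child surveys from Table 2 would leave the scale out, while someone working from the text might include it.

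**Working it through.** The plan gives no figure to reproduce here. The check is a reading of the schedule against the text.

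**Step 1: map the marks in Table 2 to its columns.**

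| Row | T1 | T2 | T3 | Close-out |
|---|---|---|---|---|
| Eligibility screen | X | | | |
| MASC and SMFQ (primary) | X | X | X | X |
| Secondary outcomes, default | X | X | X | X |
| User satisfaction, PIE, stigma sheet, implementation components | | X | | X |
| KIDSCREEN-27, RCADS and four staff measures | X | | | |
| Sustainability | | | | X |

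The T1-only reading does not come from a broken table. The mark lies in the same column as the eligibility screen, and the other rows fall where one would expect: satisfaction after the intervention, sustainability at the end. The row is also an explicit exception, which would serve no purpose if these scales followed the default.

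**Step 2: look for another quality-of-life instrument.** Table 3 has none. KINDL appears in the abbreviation list, but it is neither described in Table 3 nor scheduled in Table 2, so it cannot fill the gap.

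**Step 3: ask what the printed schedule can estimate.** For child *i*, change is Y(i, T2) − Y(i, T1) or Y(i, T3) − Y(i, T1). KIDSCREEN-27 has Y(i, T1) only, which is 0 of 2 post-baseline time points. Neither difference exists, and no comparison of conditions after the intervention can be formed. A growth curve has no slope with one wave. The planned likelihood methods for missing data do not help, because the later values would be unobserved for every child. What remains is a comparison of conditions before the intervention, which is not a factor effect.

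**Step 4: set this against the text.** The recruitment section says the same self-report measures are repeated at T3, and the data management section has children answering at T1, T2 and T3. Neither names KIDSCREEN-27. The recruitment sentence directly follows one about screening, so it may mean only the screening scales. These passages do not prove that the scale is repeated, but they leave open that the Table 2 row is the error.

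**Step 5: the two neighbouring items.**
- *RCADS.* No passage names change in the RCADS as an outcome. The Outcomes section introduces it as a free measure used alongside established instruments, with measure development in view, and the analysis section plans factor analyses, correlations and Cronbach's alpha for some instruments. One administration at T1 can serve that purpose.
- *User satisfaction.* Table 2 collects it at T2 and close-out. It cannot exist before the intervention, so only the word for change in the abstract is out of place.

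**The case against.** The strongest reply is that one table row is being read as settled design. The text on repeated child measures points the other way, and the abstract sentence is loosely drafted: it also speaks of change in user satisfaction, which cannot be meant literally. On this view either Table 2 or the abstract may simply be misprinted, and no data need be missing.

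Much of this stands. It rules out a stronger conclusion that a reader might infer, namely that quality of life and the RCADS are both wholly lost as outcomes for all of the roughly 800 children. That would follow for quality of life only if Table 2 is the correct text, which the article does not establish. For the RCADS it does not follow at all, because no change in it is promised. Its place in Table 3 is weak evidence, since that table also holds cost data, COVID-19 questions and staff questionnaires. Nor is it a design fault that satisfaction is measured only after the intervention; conditions can be compared at T2 without a baseline.

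The reply does not remove the contradiction. The abstract states the outcome, Table 2 states a schedule that cannot deliver it, and Table 2 is the only instrument-level schedule in the article. Nor can this be left to a separate analysis plan, because no analysis can use measurements that were not taken.

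**Conclusion.** The point holds as an internal contradiction. Change in quality of life is a named secondary outcome, and its only described instrument is scheduled at T1 alone, while other sections suggest that child measures are repeated. If Table 2 is followed, there are 0 of 2 post-baseline measurements and no change or factor effect on quality of life can be estimated. If the text is followed and covers KIDSCREEN-27, the outcome is intact and only the table is wrong. The documents do not say which.

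Severity is moderate. One secondary outcome is affected, and it is named as a change only in the abstract. MASC and SMFQ are scheduled at every wave. The RCADS and user satisfaction are matters of labelling.

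**What to change.** Establish what the T2 and T3 child surveys actually contain, then make the abstract, Table 2, Table 3 and the recruitment and data management sections agree. There are two ways.

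1. **Keep the outcome.** Correct Table 2 to show KIDSCREEN-27 at T2 and T3, within the child survey already given then. The cost is burden on children aged 8 to 12. Three child scales with stated lengths, MASC (39), SMFQ (13) and BSCI-Y (20), already make 39 + 13 + 20 = 72 items, and 27 more make 99, an increase of 27/72 = 37.5% on those three. If the scale was not given in earlier waves, state which cohorts contribute. By Table 2, at the protocol version date (November 2020) T2 still lay ahead for cohorts 3 to 5 and the one-year follow-up for all five. If the cohorts were of equal size (an assumption), T2 change would then rest on 3/5 × 800 = 480 of the planned children. By publication in June 2021, T2 lay clearly ahead only for cohorts 4 and 5, giving 2/5 × 800 = 320.
2. **Keep it at baseline.** Remove quality-of-life change from the secondary outcomes and call KIDSCREEN-27 a baseline measure. This costs only wording, but the trial then makes no statement on quality of life.

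In the same revision, label the RCADS as a baseline or psychometric measure if it stays at T1 only, and describe user satisfaction as a post-intervention level.
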